## **EXECUTIVE SUMMARY: ASIA PACIFIC – JD PROGRAM (WHAT, WHY & HOW)**

Diabetes is a global epidemic affecting 5-10% of the world population with China and India having the highest number of affected individuals. Diabetes reduces life expectancy by 6-12 years, if not well managed. It is the leading cause of stroke, heart disease, leg amputation, blindness and renal failure in many countries, which account for 50-60% of premature mortality and morbidity. Besides, there is increasing data suggesting close associations of diabetes with cancer and depression. Although controlling multiple risk factors improves clinical outcomes in type 2 diabetic patients, there are multiple challenges in translating evidence to clinical practice due to factors pertinent to patients, care providers and systems.

### *What is the JADE Program?*

Since mid 1990s, the CUHK Diabetes Care & Research Group and others have advocated the use of a team comprising a doctor, nurse and health care assistant (HCA) to deliver protocol-augmented collaborative care. The key components of this collaborative care model include risk stratification, periodic assessments, reinforcement of compliance and control of multiple risk factors. These prototypes substantially improve rates of treatment compliance and attainment of multiple treatment targets resulting in reduced risks of death and cardiovascular-renal complications.

In 2007, supported by an educational grant, a charitable organization named the Asia Diabetes Foundation (ADF) ([www.adf.org.hk](http://www.adf.org.hk)) was established under the Chinese University of Hong Kong (CUHK) Foundation. The mandate of ADF is to develop and implement the Joint Asia Diabetes Evaluation (JADE) Program, which comprises a web-based disease management program to enable doctors, nurses and care professionals to manage people with diabetes in an integrated manner and to establish a diabetes registry for quality assurance purpose.

### *Why do we need the JADE Program?*

In line with the recommendation by the International Diabetes Federation, the JADE electronic portal (e-portal) provides a virtual platform to facilitate implementation of evidence-based clinical protocols with ongoing data collection, management and analysis. The JADE Program incorporates validated risk equations developed by the CUHK Diabetes Care & Research Group for risk stratification and triage into different care protocols with

decision supports. This data is communicated to patients and care providers in the forms of charts and time trends to motivate behavioral changes and encourage collaborative goal setting and attainment.

#### How to implement the JADE-DIAMOND (JD) Program?

By participating in the JADE Program, doctors will be able to create their own diabetes registry for quality assurance and benchmark their performance including adherence to procedures, tracking of default rates and attainment of treatment targets. However, effective implementation of the JADE Program requires changes in practice environment and additional manpower (e.g. a nurse) to collect clinical data systematically, maintain a database and remind patients and doctors to adhere to protocols. As the first step towards this quality improvement program, structured templates can be used to guide care professionals to collect data systematically during comprehensive assessment to form a DIAbetes MONitoring Database (DIAMOND) for early detection of risk factors and complications.

#### Objectives and expected outcomes of AP -JD Program

In this demonstration project (Asia Pacific JADE and DIAMOND Program, AP-JD in short) supported by ADF, patients will be recruited from different sites across Asia, with each site recruiting at least 600 type 2 diabetic patients. After explanation by trained doctors and nurses, and with written informed consent, patients will be randomized to either the JADE (n=300, structured care) or DIAMOND (n=300, usual care) group. All patients will undergo a comprehensive assessment (CA) at baseline and yearly thereafter. Patients in the JADE group will be further managed by a doctor-nurse-HCA team according to a protocol based on risk stratification with predefined follow up (FU) schedules together with shared information and decision support (i.e. structured collaborative care). The DIAMOND protocol involves only baseline and yearly CA without predefined FU schedules or feedback of information between CA visits (i.e. usual care). The primary composite endpoint is all-diabetes related clinical endpoints. The secondary composite endpoint is attainment of treatment goals and/or control of risk factors. The tertiary changes are behavioral changes, psychological well being and quality of life.

**ABSTRACT**

**Rationale:** Change of practice environment and an interdisciplinary team is needed to implement evidence-based diabetes care which requires risk stratification, periodic assessments, education and treatment to targets.

**Hypothesis:** The use of a web-based disease management program (Joint Asia Diabetes Evaluation (JADE) Program) delivered by a doctor-nurse-HCA team reduces the incidence of all diabetes-associated clinical endpoint and improves control of risk factors compared to usual care (DIAbetes MONItoring Database (DIAMOND) group) in type 2 diabetes.

**Objective:** To compare structured care using the JADE portal versus usual care using the DIAMOND portal on incidence of all-diabetes related events, physical and psychological health.

**Study design:** A multicentre, randomized, integrated disease management program

**Setting and patients:** 600 patients from each site will be randomized to the JADE group (n=300) or the DIAMOND group (n=300) and followed up for at least 24 months.

**Intervention:** All patients will undergo comprehensive assessment (CA) guided by the templates in the respective portal at baseline, month 12 and 24. The JADE group will be further managed by a doctor-nurse-HCA team guided by the JADE portal with risk stratification program and recommendation to different care protocols with predefined follow up (FU) schedules, information sharing and decision supports.

**Outcome measures:** Primary composite outcomes include all diabetes-related clinical events; secondary composite outcomes include control of risk factors and tertiary composite outcomes include behavioral changes, psychological health, quality of life and cost-effective analysis.

## BACKGROUND

### Type 2 diabetes in Asia

Diabetes is now a pandemic disease affecting 5-10% of global population. More than 60% of affected people will come from Asia and the number is expected to increase from 85 million in 2005 to 132 million in 2010 in Asia alone (1). On average, diabetes reduces life expectancy by 6-12 years, if not well managed (2; 3). While stroke, heart disease and kidney failure account for more than 50% of global deaths, 30-50% of patients with these conditions have diabetes as a major causal factor (4). In contrast to the West, the main increase in diabetes prevalence in Asia will occur in the young to middle aged population (5; 6). In 2005, it was estimated that 17 million of deaths were due to stroke and heart disease, of which 11 million occurred in Asia, affecting many young parents and economically active people (7).

### Structured care

Despite their devastating nature, many diabetic complications can be prevented, controlled and managed effectively to preserve health, reduce disabilities and improve quality of life. However, there are multiple barriers in the implementation of quality diabetes care which include periodic evaluation of clinical and laboratory parameters as well as support for people with diabetes to adhere to long term medications and self care. Due to the silent nature of diabetes and associated complications as well as the complex nature of care protocols, clinical inertia and poor compliance are not uncommon. Apart from the need to build capacity and strengthen the health care system to provide integrated care, lack of incentives and reimbursement for outpatient procedures including therapeutic patient education are other barriers in delivering quality chronic care (8-12).

Thus, although treatment to targets for risk factors can substantially reduce the risk of diabetes associated complications (13-18) especially in a clinical trial setting (19), the challenge lies in translating this evidence to daily practice. Since mid-1990s, inspired by the benefits of structured care, made possible during the conduct of clinical trials (20; 21) and in line with the results from metaanalysis (22-24) and international recommendations including that by the International Diabetes Federation (25; 26), the CUHK Diabetes Care & Research Group has developed structured care prototypes including regular comprehensive assessments (CA) implemented by a doctor-nurse-HCA team. In agreement with international data, these prototypes substantially improved rates of treatment compliance and attainment of multiple

treatment targets resulting in reduced death, cardio-renal complication and hospitalization rates (27-33).

IDF Global Guideline for care delivery

**International Diabetes Federation Global Guidelines**  
**Recommendations for diabetes care delivery**

**Standard care**

- CD1 Offer care to all people with diabetes, with sensitivity to cultural wishes and desires.
- CD2 Encourage a collaborative relationship, by actively involving the person with diabetes in the consultation, and creating opportunities for them to ask questions and express concerns. Ensure that issues important to the person with diabetes are addressed.
- CD3 Offer annual surveillance of all aspects of diabetes control and complications to all people with Type 2 diabetes
- CD4 Agree a care plan with each person with diabetes, review this annually or more often if appropriate and modify it according to changes in wishes, circumstances and medical findings.
- CD5 Use protocol-driven diabetes care to deliver the care plan between annual reviews, at booked routine reviews.
- CD6 Provide urgent access to diabetes health-care advice for unforeseen problems.
- CD7 Organize care around the person with diabetes.
- CD8 Use a multidisciplinary care team with specific diabetes expertise maintained by continuing professional education.
- CD9 Ensure that each person with diabetes is recorded on a list of people with diabetes, to facilitate recall for annual complications surveillance.
- CD10 Provide telephone contact between clinic visits.
- CD11 Consider how people with diabetes, acting as expert patients, and knowing their limitations, together with local/regional/national associations, might be involved in supporting the care delivery of their local health-care team.
- CD12 Use data gathered in routine care to support quality assurance and development activities.

**Comprehensive care**

- CDC1 In general this would be as *Standard care*.
- CDC2 The person with diabetes will have access to their own electronic medical record via secure technology from remote sites. They will be able to give permission for any health-care professional to access that record.
- CDC3 Decision support systems might be available to the health-care professional and perhaps to the person with diabetes.

**Minimal care**

- CDM1 Offer annual surveillance, agree care plans, deliver protocol-driven care, and ensure that each person with diabetes is recorded on a local list of people with diabetes, as for *Standard care*.
- CDM2 Organize care around the person living with diabetes, using an appropriately trained health to deliver the diverse aspects of that care

**JADE Program**

The JADE Program is a web-based disease management program conceptualized, developed and tested by the ADF since 2007 supported by a MSD educational grant (34-36). The objectives of the JADE Program are to:

- 1) promote collective learning and sharing of best practices in diabetes based on regionally relevant evidence.
- 2) increase regional awareness about the magnitude of diabetes and its preventable nature through education, ongoing data collection and implementation of evidence-based care.
- 3) establish a regional diabetes registry
  - a) to improve our understanding of disease progression including identification of novel risk factors for diabetes and associated complications.
  - b) to monitor levels of adherence to recommended procedures and care processes by people with diabetes and care providers and their changes over time.
  - c) to document the patterns of care and levels of attainment of recommended treatment targets and their changes over time.

- d) to evaluate the impacts of interventions including use of medications and care protocols on clinical outcomes and their relative cost-effectiveness.
  - e) to foster inter-sectoral, inter-disciplinary and inter-institutional collaborations to achieve these inter-linked objectives.
- 4) collect the evidence and inform relevant stakeholders including general public, people with diabetes, healthcare professionals, policy makers and payers, to change policies and practices in order to make quality diabetes care accessible, sustainable and affordable.

Using *state of the art* information technology, the JADE electronic portal provides a virtual platform to enable care professionals to record, manage and analyze the large amount of information collected during various consultation visits. The JADE Program also incorporates risk equations developed and validated by the CUHK Diabetes Care & Research Group to help doctors assess their patients' future event rates (37). This information, displayed in charts and trend lines, aims to motivate behavioral changes and promote dialogues between patients and care providers to set and attain mutually agreeable treatment goals (35).

[figure not shown]

Apart from providing templates for documentation of risk factors and complications using standardized protocols, the JADE Program also incorporates different evidence-based care protocols with recommendations on FU schedules and care processes in accordance to the patient's risk profile. Decision support in terms of prompts, charts, trend lines and practice tips are used to help doctors and patients make informed decisions and optimize care. The JADE Program also possesses matrixes which enable care providers to track clinical progress

and risk factor control for benchmarking and quality improvement purposes. On the other hand, the DIAMOND Program represents the first step towards a quality assurance program by enabling the doctor to collect data during CA at regular intervals to establish a diabetes registry. The ongoing data collection provides an invaluable platform for collaborative epidemiological and interventional studies pertinent to Asian populations (35).

## **HYPOTHESIS**

Delivery of quality diabetes care requires a team approach with informed decisions from patients and care providers. Several lines of evidence suggest that a protocol-augmented collaborative care model with particular focus on periodic assessments, reinforcement of patient compliance and attainment of multiple treatment targets reduces risk of cardiovascular-renal complications and premature death in type 2 diabetes.

We hypothesize that the use of *state of the art* information technology to record, manage and analyze clinical information collected during consultation visits improve the effectiveness and efficiency in implementing these care protocols through decision support and regular feedback to both patients and care team.

We further hypothesize that structured care using the JADE Program delivered by an interdisciplinary team will be more effective than usual care (DIAMOND) Program in controlling multiple risk factors, reducing clinical event rates and improving quality of life.

## **OBJECTIVES**

In this 2-year multicentre, randomized integrated disease management program, we shall use a web-based disease management program to guide comprehensive assessment with or without risk stratification and clinical protocols and to compare the effectiveness of the JADE (structured care) versus DIAMOND Programs (usual care) in

- 1) reducing all diabetes-related clinical endpoints
- 2) control of multiple risk factors
- 3) improving quality of life, psychological well-being and health behaviors.

## **STUDY DESIGN**

This is a multicentre, randomized integrated disease management program to compare the effects of structured care using the JADE portal versus usual care using the DIAMOND portal on incidence of all diabetes-related clinical endpoints in a naturalistic setting.

Ethical approval will be obtained from the local institutional board before commencement of the study. The doctor will explain to eligible patients the rationale for undergoing regular CA to detect silent risk factors and complications and the need to assess the cost-effectiveness of using a team to deliver structured care and empower self-management. With written informed consent and after randomization, a trained nurse will perform the CA using structured protocols in all patients at baseline, 12 and 24 months, further assisted by the doctor and HCA. All patients will be asked to complete simple questionnaires to assess psychological health, quality of life and behaviour during CA visit. The trained nurse will perform simple procedures (e.g. measurement of anthropometric indexes, visual acuity, blood pressure (BP), blood drawing and collecting urine samples).

Apart from assisting the nurse, the HCA will be responsible for entering data, managing the database and maintaining an appointment and filing system. The doctor will focus on taking medical history to diagnose, identify needs and monitor clinical progress. The doctor will also perform eye and feet, and any other relevant, examinations or refer patients to appropriate personnel to undergo these assessments during the CA. All data will be first captured using case report form (CRF) during CA and FU visits followed by data entry. Patients randomized to the JADE group will be followed up 2-4 monthly by a doctor-nurse-HCA team using predefined protocol in group review clinics in order to facilitate group education and promote peer interactions. We expect a doctor-nurse-HCA team to screen 4-6 patients daily and recruit 600 patients within 6-8 months from each centre, giving a total FU period of 2.5-3 years.

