2) Proportions of patients with improved control of risk factors defined as:

- a) 2 or more of the ‘ABC’ targets:
  - i) HbA1c < 7%
  - ii) BP < 130/80 mmHg
  - iii) LDL-C < 2.6 mmol/L
- b) and/or
- c) 2 of the following changes in risk factor control:
  - i) at least 0.5% reduction in HbA1c
  - ii) at least 5 mmHg reduction in systolic BP
  - iii) at least 0.5 mmol/L reduction in LDL-C
  - iv) at least 3% reduction in body weight

Composite tertiary endpoint

- 3) Quality of life (ED-5Q)
- 4) Frequency of hypoglycaemia (in the last 3 months) as recorded in the JADE CA form
- 5) Behavioral changes in last 3 months as recorded in the JADE CA form
  - a) Frequency of Self Blood Glucose Monitoring
  - b) Adherence to balanced eating
  - c) Adherence to regular exercise
- 6) CQ4 for compliance
- 7) PHQ-9 for depression
- 8) Hospitalization days and cost-effectiveness analysis
- 9) Additional questionnaires are available for interested investigators to assess other psychological parameters (self efficacy, diabetes related stress, perception of happiness, personal habits) and self-care activities to explore reasons which may explain differences in outcomes between the 2 groups (see appendix).

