### Randomization

Computer-generated codes numbered 1 to 600 with assignment to either JADE or DIAMOND group will be prepared by ADF for each site. Three sets of envelopes with equal assignment to JADE or DIAMOND Group will be given to the study site at regular time intervals depending on rate of recruitment. The randomization procedures are as follows:

- 1) The doctor or nurse will explain to eligible patients regarding the international recommendation on performing regular CA to detect silent risk factors and complications.
- 2) They will also explain to patients the need to assess cost-effectiveness of using a team to implement structured care by comparing the latter with usual care.
- 3) After the patient has signed the consent, a staff not participating in the study will open the envelope containing the randomization group and sign and date the envelope.
- 4) The signed envelope will be kept by the nurse in a secure place for audit purpose.
- 5) The nurse will explain to patient whether they have been randomized to JADE or DIAMOND and the assessment will proceed accordingly.
- 6) The nurse will fax the randomization form to the ADF office and keep a log of randomized patients and record status including study completion, premature discontinuation, consent withdrawal or lost to follow up.
- 7) The doctor or nurse will contact the ADF to obtain the user code to enrol the patient in either the JADE or DIAMOND portal and obtain a patient identification number (ID).

[figure not shown]

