### Secondary composite outcome

In a 1-year pilot study, 240 high risk Chinese T2D patients with CHD or multiple risk factors who have undergone CA using the JADE portal were randomized to usual care or structured

care group. In the latter group, supported by an endocrinologist and guided by a protocol, a diabetes nurse, assisted by a HCA, reviewed these patients every 3 to 4 months in addition to receiving usual care. At the end of 1 year, there were significant reductions in all risk factors in both groups, but more so in the team-based structured care group. The rate of attaining at least 2 of the 3 'ABC targets' increased by 2.5 fold from 15% to 37% in the structured care group while respective figures in the usual care were 20% to 28% with 1.4 fold increase, giving a 2 fold difference between the 2 groups. In the Hong Kong Diabetes Registry, type 2 diabetic patients who attained 2 of the 3 'ABC' targets had 50% risk reduction in incident CHD after a mean follow up period of 6 years (40).

| Change in risk factors at 1 year      | HbA1c (%) |    | Systolic BP (mmHg) |    | LDL-C (mmol/l) |    | body weight (%) |     |
|----------------------------------------------|-----------------------------|----|---------------------------|----|-----------------------|----|------------------------|-----|
| Effect size (reduction compared to baseline) | 0.5                         | 1  | 5                         | 10 | 0.5                   | 1  | 3                      | 5   |
| Structured care (%)                          | 77                          | 61 | 46                        | 35 | 32                    | 16 | 16                     | 8.7 |
| Usual care (%)                               | 60                          | 44 | 29                        | 18 | 26                    | 9  | 6                      | 2.6 |
| Between group Difference (%)                 | 17                          | 17 | 17                        | 17 | 6                     | 7  | 10                     | 6   |

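### The baseline assessment follows disclosure of the group, so baseline blood pressure, weight, examinations, history and questionnaires are recorded with the arm known

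*Protocol*

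**What the plan says.** The order of steps is explicit and consistent in three places of the Protocol.

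- Study Design: "With written informed consent and after randomization, a trained nurse will perform the CA using structured protocols in all patients at baseline", and again at 12 and 24 months.
- Randomization, step 3: "After the patient has signed the consent, a staff not participating in the study will open the envelope containing the randomization group". Step 5: "The nurse will explain to patient whether they have been randomized to JADE or DIAMOND and the assessment will proceed accordingly". The portal code is obtained last, in step 7.
- Abstract, Intervention: the comprehensive assessment (CA) is "guided by the templates in the respective portal at baseline, month 12 and 24", so as written the baseline CA depends on the assigned arm.

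Study Design also says who measures what: "The trained nurse will perform simple procedures (e.g. measurement of anthropometric indexes, visual acuity, blood pressure (BP" and so on. The doctor takes the history and performs, or refers for, the eye and foot examinations. Patients complete the quality-of-life, CQ4 and PHQ-9 questionnaires at the CA (Comprehensive assessment, item 7).

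The composite secondary endpoint (Outcome Measures) has two routes. Part (a) is attainment of two or more ABC targets. Part (c) is two of four reductions, including "at least 5 mmHg reduction in systolic BP" and "at least 3% reduction in body weight". The sample size table for these reductions takes baseline as the reference. The primary endpoint is an incidence and includes visual impairment and eGFR below 60.

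**The concern.** A reduction is the baseline reading minus a later reading. If the baseline reading depends on the arm, the reduction carries that dependence whatever the later reading shows. Here the nurse and doctor know the arm when they record baseline, and they belong to the team that will treat the JADE patients. The patient also knows the arm before answering the questionnaires. The bias need not be deliberate: repeating a high reading, rounding, or probing further for symptoms in one group is enough.

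Two further consequences follow. A condition that is searched for less carefully at baseline in one arm can later be counted there as new. And a patient who leaves on hearing the allocation may have no baseline record, so selective loss between the arms could not be described.

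**Working it through.** **1. Sequence.** Study Design, Randomization and the Abstract give the same order: consent, envelope, disclosure, baseline CA. No section places any baseline measurement before allocation or provides a masked assessor.

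**2. Which items are exposed.**
- Exposed: blood pressure, weight, visual acuity, eye and foot examination, complication history, questionnaires.
- Little exposed: HbA1c, LDL-C and eGFR, which are laboratory values. Chronic kidney disease is defined by eGFR alone.
- Independent of baseline: part (a) of the secondary endpoint, which uses absolute thresholds.
- Mostly independent of baseline readings: deaths, hospitalised events, amputation and surgery.

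**3. The plan's own figure.** For a systolic fall of at least 5 mmHg the plan has 46% against 29%, two-sided 0.05, 80% power and 138 per group.
- Uncorrected: n = [1.96√(2 × 0.375 × 0.625) + 0.8416√(0.46 × 0.54 + 0.29 × 0.71)]² / 0.17² = (1.342 + 0.567)² / 0.0289 = 126.1, that is 127.
- With continuity correction: (126.1/4)[1 + √(1 + 4/(126.1 × 0.17))]² = 137.6, that is 138. The figure reproduces, and moving the baseline CA would not change it.

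**4. Illustration for the systolic component.** The Protocol gives no standard deviation (SD) for the change in pressure. Assumed: change is normal with SD 12 to 18 mmHg and mean μ of 0 or −5. An arm difference δ in recorded baseline moves the responder share by Φ((−5 − μ + δ)/SD) − Φ((−5 − μ)/SD).
- δ = 1, smallest (μ = 0, SD 18): Φ(−0.222) − Φ(−0.278) = 2.1 points.
- δ = 1, largest (μ = −5, SD 12): Φ(0.083) − Φ(0) = 3.3 points.
- δ = 2, same cases: 4.3 and 6.6 points.

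These settings imply responder shares of about 34% to 50%. Calibrating to the planned 29% changes little (about 1.9 to 2.9 points per mmHg).

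**5. Carried to the actual composite.** Systolic pressure decides part (c) only when exactly one of the other three reductions is met. Take the pilot usual-care rates (HbA1c 60%, LDL-C 26%, weight 6%) and assume independence:

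0.60 × 0.74 × 0.94 + 0.40 × 0.26 × 0.94 + 0.40 × 0.74 × 0.06 = 0.533.

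Patients already counted under part (a) drop out: 28% in the pilot's usual-care group, or 45% in the middle planning case.
- Share affected: 0.533 × 0.72 = 0.384, or 0.533 × 0.55 = 0.293.
- δ = 1: from 2.1 × 0.293 = 0.6 to 3.3 × 0.384 = 1.3 points.
- δ = 2: from 4.3 × 0.293 = 1.3 to 6.6 × 0.384 = 2.5 points.

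**6. Against sampling error.** For one site with 300 per arm and a composite rate near 50% (assumed), the standard error of the difference is √(2 × 0.25/300) = 4.1 points. A bias of 0.6 to 2.5 points is 0.15 to 0.61 standard errors. With no true effect, the chance of a significant result favouring JADE is then 1 − Φ(1.81) = 3.5% to 1 − Φ(1.35) = 8.9%, against 2.5% nominal. Pooling sites shrinks the standard error but not the bias.

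**The case against.** The strongest reply is that this is an open trial in a naturalistic setting, that nothing shows a difference in baseline recording, and that the 1 to 2 mmHg has no source in the Protocol. All of that stands: the point is an avoidable risk, not a demonstrated bias.

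Several stronger readings are tempting and are not supported.
- *HbA1c reductions and incident kidney disease are biased too.* Both rest on laboratory values, which an assessor who knows the arm does not change.
- *The 2 to 7 points are the error in the secondary endpoint.* They apply to one component, which is not an endpoint by itself. Step 5 of the working gives the smaller composite figure. A weight bias could add to it and is not quantified here.
- *No adjustment can remove the problem.* The covariates named for the primary comparison (age, sex, ethnicity, disease duration) are hardly open to arm-dependent recording, and an analysis of final values would not use the baseline reading.
- *Every patient who leaves after allocation is lost.* The assessment is meant to follow directly. For the primary endpoint one telephone contact suffices, and consent covers such contact.
- *The plan contradicts itself, because patients "who have undergone CA using the JADE portal were randomized to usual care or structured" care.* That sentence describes the earlier pilot. It shows that the other order is workable, not that this trial promises it.

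The adjudication committee helps with reported events, but its stated task is to review event narratives and supporting documents. Baseline status is not mentioned.

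**Conclusion.** The concern holds in limited form. The Protocol fixes a sequence in which observer- and patient-dependent baseline items are recorded with the arm known, by staff who also deliver the intervention. The parts at risk are the systolic pressure and weight reductions in part (c) of the secondary endpoint, changes in tertiary questionnaire scores, and the existing-versus-new status of some primary components such as visual impairment.

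The size is modest: about 0.6 to 2.5 points on the secondary composite for a 1 to 2 mmHg arm difference. That rests on an assumed SD of change of 12 to 18 mmHg, a mean change of 0 to −5 mmHg, pilot response rates and independence between components. The direction of any bias is not known. The case for changing the plan rests on how cheaply the risk can be removed, not on a large expected distortion.

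**What to change.** In Study Design and Randomization, set the order as follows:

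1. Written consent.
2. Full baseline CA on one common paper form: history, blood pressure, weight, eye and foot examination, blood and urine samples, questionnaires.
3. Envelope opened and signed, and the group disclosed.
4. Enrolment in the JADE or DIAMOND portal.

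Amend the Intervention paragraph of the Abstract so that the baseline CA uses a common template rather than that of the assigned portal. This fits current practice: data already go to a paper form before portal entry, and the portal code is already obtained last.

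The cost is small, with no extra staff and no change in sample size. A few patients who consent but do not complete the CA will not be randomised. Because the CA requires at least 8 hours of fasting, consent and assessment may fall on different days. The change protects the baseline only: no masking is stated for the 12- and 24-month assessments, and their blood pressure, weight and questionnaire data stay open to the same influence.
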